**Data collection and management**

SAS© computer software will be used to create a database. FSEDIT (SAS) will be used to maintain the database. Responses will be entered into the database as they become available using double data entry to minimize key stroke errors. Data cleaning will occur on an ongoing basis.

**Statistical Analysis**

*Power calculations*

[figure not shown]
Power calculations performed using the xsampsi application for sample size and power in crossover trials (Stata v. 11.0) were used to create the figure below. Assuming 10 unique individuals are recruited into the study, we will have 70-80% power to detect mean changes of between 0.5 and 1.5 points on a 5 point Likert scale, under different assumptions regarding the standard deviation in such measurement (SD 0.5, 1, 1.5 or 2). As such, we expect to be able to detect clinically meaningful changes in measurement with treatment even with the relatively small sample size anticipated in this pilot study. Data collection will permit further refinement of power and sample size calculations for future, larger trials if effects observed here are promising.

*Statistical Analysis*

Because of between patient variability in the affected area injected and severity of paratonia, and because of our desire to control for period and ordering effects we will use mixed regression models for analyses of quantitative outcomes, in order to isolate the effect of Botulinum toxin relative to placebo. Mixed models as applied to crossover designs permit adjustment for treatment sequences (i.e., Botulinum toxin first vs. second), period effects (i.e., first injection vs. second injection), between individual variation in severity and response to therapy, etc. We will estimate treatment fixed effects (i.e., effect of Botulinum toxin treatment), defined as the change in relevant scores from baseline to 6 weeks, and 16 to 22 weeks (i.e., change from baseline until 6 weeks post-treatment or placebo). Because of the anticipated variability in severity of paratonia in individual patients, and variability in responses of caregivers to patient disability, we will treat individual patient/caregiver dyads as model random effects.

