*Outcome measures*: The primary outcome measure will be the Carer Burden Scale assessing ease of administering care that includes aspects of providing hygiene and dressing. Secondary outcome measures will include the Modified Ashworth Scale (MAS) objectively measuring increased tone, time taken to perform tasks (morning care routine) before and after treatment, and the caregiver Visual Analogue Scale (VAS) assessing perception of ease of care-giving, nurse-investigator and professional and caregiver Global Assessment Scale (GAS) assessing overall response to treatment. The Pain Assessment in Advanced Dementia (PAINAD) instrument will be used to assess whether treatments reduce pain in patients when having morning care performed. Video-recordings of morning care routines prior and following treatments will be reviewed and compared to ensure reliability. Additionally, the caregiver will be questioned in an open-ended format to determine what additional factors contributed to relevant changes in the care of patients as a result of the injections that may not have been captured with quantitative measures.

**Statistical Analysis:** The proposed crossover design warrants the use of mixed regression modeling techniques in order to isolate the effect of Botulinum toxin, relative to placebo on the described outcomes. Treatment effects will be defined as the change in relevant scores from baseline to 6 weeks, and 16 to 22 weeks (i.e., change from baseline until 6 weeks post-treatment or placebo).

**Conclusions:** In these times of fiscal constraint, difficult decisions regarding resource allocation to optimize patient care need to be made. An intervention with the capacity to reduce care burden, improve standard of care, and potentially increase patient and caregiver quality of life, would be an attractive strategy. Preliminary experience suggests that Botulinum toxin injections may result in this effect. This pilot study will assess the feasibility of conducting a larger study that will evaluate the impact and cost-effectiveness of reduction of tonein cognitively impaired, fully dependent individuals.

.

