**Pilot study objectives**

*Primary Objective*:

1. Confirm proof of principle that paratonic rigidity and its consequences can be reduced with Botulinum toxin injections resulting in reduced caregiver burden.

*Secondary Objectives:*

1. Determine optimal time points for evaluation of efficacy in this patient
   population and whether this time period is sufficient for washout of Botulinum toxin effect
2. Determine most salient and sensitive outcome measures
3. Identify obstacles in data gathering
4. Determine feasibility of battery of assessments in this pilot study that will eventually be used in a future phase III study

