**DEVIATION OF FINAL MANUSCRIPT FROM PROTOCOL SUBMITTED TO REB**

***This data was collected but it became clear that this method of determining time it takes to accomplish morning routine was not feasible. There were different people performing morning care at each assessment in different ways and with variable efficiency despite trying to ensure prior to emrolment that this was uniform. For “time to perform morning care” to become a valid measure it would be necessary to standardize the protocol for administering care and by the same individual. As this study was a pilot study also looking at feasibility, we recognized that the way we collected this did not provide meaningful and valid data and chose to omit from our reporting. A future study on a larger scale (if performed) would need to consider these factors and record the time variable in a different way.***

1. **Visual Analogue Scale:** A caregiver burden visual analogue scale (VAS) will be completed by the professional caregiver caring for the patient in order to assess perception of ease of caregiving (16). A VAS will be used because it has been found to be valid in capturing subjective perceptions of health-related quality of life and other qualitative health outcomes (24). The VAS consists of a 100 mm line with anchors of 0 “giving care to the residents is very difficult” and 100 “giving care to the residents is very easy”.
2. **Global Assessment**: Overall response to treatment will be evaluated by the study investigator and by the professional caregiver caring for the patient using the global assessment scale (26) at each follow-up visit. A score of -4 indicates very marked worsening, 0 no change, and +4 very marked improvement.
3. **Pain:** As patients with advanced dementia are not able to express their experience of pain, a surrogate measure, the Pain Assessment in Advanced Dementia (PAINAD) Scale (25) will be used by the study nurse at each assessment time point to objectively evaluate correlates of pain and determine whether treatment with Botulinum toxin reduces the discomfort experienced during morning care. The PAINAD scale consists of 5 items (breathing, negative vocalization, facial expression, body language, and consolability) scored on a 0-2 point scale and then summed to arrive at a total score. The score will be averaged over 2 days

*Qualitative Assessments*

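### Subtracting each cycle's own baseline can cost precision in this 10-patient crossover and makes the estimate depend on toxin effect fading after week 16; use the baseline difference as a covariate instead

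*Protocol*

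**What the plan says.** The definition appears twice. The Project Summary gives it in outline. The Statistical Analysis section gives it again for the fixed treatment effect of a mixed model, which can adjust for sequence and period: the effect is "defined as the change in relevant scores from baseline to 6 weeks, and 16 to 22 weeks". On the random part, that section adds: "we will treat individual patient/caregiver dyads as model random effects". The baselines are subtracted rather than used as covariates, and no carry-over term is named.

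On washout, the Outcomes section justifies 16-week cycles by expecting no residual effect at that point, and the Rationale puts the duration of effect at about three months. The secondary objectives nevertheless ask "whether this time period is sufficient for washout of Botulinum toxin effect".

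The Global Assessment is rated "using the global assessment scale (26) at each follow-up visit", on a scale from -4 (marked worsening) through 0 (no change) to +4 (marked improvement).

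The power statement begins: "Assuming 10 unique individuals are recruited into the study, we will have 70-80% power". The target is an effect of 0.5 to 1.5 points on a five-point item scale, and four SDs between 0.5 and 2 are considered. The text does not say whether that SD belongs to a score, a change or a within-patient difference, and it gives no significance level, sidedness or correlation.

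**The concern.** Baseline subtraction helps in a parallel-group trial because it removes differences between patients. Here the patient is already compared with himself or herself, so the two baselines may contribute mainly their own measurement error. With 10 patients there is little precision to spare.

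The second baseline is also not a clean one. In the toxin-first sequence, week 16 is a post-toxin measurement. If some benefit remains then and disappears by week 22, the placebo cycle shows a deterioration that the contrast credits to toxin. Period and sequence terms do not remove this. The main estimate would then depend on a question that the pilot itself sets out to answer.

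**Working it through.** **Inputs.** From the protocol: 10 patients, two sequences, scores at weeks 0, 6, 16 and 22, effects of 0.5 to 1.5 points, SD 0.5 to 2. Assumed, because the protocol does not give them: 5 patients per sequence, two-sided 5% level, and all correlations.

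**The plan's own figure.** The 70-80% power cannot be strictly reproduced from the text. Reading the SD as that of the within-patient difference, with SE = SD/√10 and a t-test on 8 df, the differences detectable with 70-80% power are:
- SD 0.5: 0.45-0.51
- SD 1: 0.90-1.01
- SD 1.5: 1.34-1.52
- SD 2: 1.79-2.02

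So the stated range of 0.5 to 1.5 points fits SDs of 0.5 to 1.5. Nothing below depends on this reading.

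**Variance.** Let s² be the variance of a score, rw the correlation of two visits within a cycle (weeks 0 and 6, or 16 and 22), and rb a common correlation of visits in different cycles. Per patient:
- Post scores: Var(Y6 - Y22) = 2s²(1 - rb)
- Change scores: Var[(Y6 - Y0) - (Y22 - Y16)] = 4s²(1 - rw)
- Ratio, change to post: 2(1 - rw)/(1 - rb)

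If rw = rb, as a dyad random intercept on the scores implies, the ratio is exactly 2. With rb = 0.5 it is 1.6 at rw = 0.6 and 0.8 at rw = 0.8. With a random intercept plus serial correlation over six weeks of 0.2, 0.4, 0.6 and 0.8, it is 1.67, 1.40, 1.17 and 0.95.

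**Power.** Take s = 1, effect 1, 10 patients and equal correlation 0.6. The change-score variance is 4 × 0.4/10 = 0.16 and the post-score variance is 2 × 0.4/10 = 0.08. Simulation of 20,000 crossovers gives 0.160 and 0.080, and 0.093 for post scores with the baseline difference as covariate.

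| Assumed correlation | Change | Covariate | Post only |
|---|---|---|---|
| 0.6 throughout | 60% | about 80% | 87% |
| 0.75 within cycle, 0.54-0.66 across | 75% | 84% | 85% |
| 0.85 within cycle, 0.64-0.78 across | 93% | 95% | 94% |

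In four further correlation structures the covariate model was no less precise than change scores (variances 0.085 v 0.105, 0.055 v 0.064, 0.019 v 0.021, 0.058 v 0.064).

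**Effect on the plan's power.** If the stated SD is that of the post-score difference and the variance doubles, power for an effect of one SD falls from 79.1% to 50.2% (t, 8 df), and the difference detectable with 80% power rises from 1.01 to 1.43 SD. If the stated SD already describes the difference between changes, the stated power does not fall.

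**Carry-over.** Let tau be the true benefit, and L16 and L22 the residual toxin benefit at weeks 16 and 22 in the toxin-first sequence. That sequence's change contrast is tau + (L16 - L22); the other sequence gives tau. Averaging over sequences:
- Change scores: tau + (L16 - L22)/2
- Post scores: tau - L22/2

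With tau = 1:

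| L16 | L22 | Change | Post only |
|---|---|---|---|
| 0.25 | 0 | 1.125 | 1.00 |
| 0.4 | 0 | 1.20 | 1.00 |
| 0.4 | 0.2 | 1.10 | 0.90 |
| 0.4 | 0.4 | 1.00 | 0.80 |

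The covariate model subtracts only a fraction of the baseline difference, so it lies between the two. In simulation it gave 1.045-1.073 for L16 = 0.25, L22 = 0 (about 35-60% of the change-score bias), and 0.91-0.95 when the residual was 0.25 at both weeks, against 0.87 for post scores.

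**The case against.** Change from period baseline is a recognised crossover analysis, and four objections to criticising it carry weight.

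- A reader might infer that any incomplete washout exaggerates the benefit. It does not: the bias depends on the residual fading between weeks 16 and 22. With a constant residual the protocol's rule is the unbiased one, and post scores understate the effect. This objection stands in full.
- A reader might infer that half the information is always lost. That requires visits 6 weeks apart to correlate no better than visits in different cycles. The protocol gives no correlation, and the plausible range includes no loss. This also stands.
- Using the week-16 value as a covariate does not escape carry-over, because it is still a post-toxin measurement. This stands, which is why the covariate model needs two sensitivity analyses beside it.
- The carry-over is hypothetical. On the protocol's figures the effect lasts about three months against a 16-week cycle, and a bias of 0.125 is small beside standard errors of about 0.24 to 0.40. That limits the size of the concern but does not remove it, since the protocol lists washout as unresolved.

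On the Global Assessment, a reader might infer that the rule demands an impossible subtraction, as there is no week-0 rating. The protocol does not go that far: the reference to relevant scores can be read as excluding a scale that is already a change rating. The point is a minor clarification.

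**Conclusion.** The concern holds in a conditional form. The protocol fixes a contrast whose variance can be up to twice that of the week-6 against week-22 comparison when all visits are equally correlated. At an assumed correlation of 0.6 that means power of about 60%, against 80% with a baseline covariate. There is little or no loss at a within-cycle correlation of about 0.85, given the cross-cycle correlations of 0.64 to 0.78 assumed with it.

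The change-score estimate is also shifted by (L16 - L22)/2. The shift is upward only if residual benefit fades between weeks 16 and 22. If washout is complete by week 16, only the precision point remains. The planned estimator is therefore not invalid. It is inefficient under plausible correlations and exposed to a question the trial leaves open.

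**What to change.** Replace the definition with: the week-6 and week-22 scores are the response, in a model with treatment, period and patient effects and with the within-patient difference between the two cycle baselines as covariate.

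Report two sensitivity analyses: post scores without any baseline, and change from each cycle's baseline. In expectation they bracket the true effect as long as the residual benefit does not grow between weeks 16 and 22. State that the covariate model does not remove carry-over bias. Analyse the Global Assessment as rated at weeks 6 and 22, without subtraction.

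The cost is a few sentences in the analysis section and one degree of freedom; every score needed is already scheduled. The document itself records that results have been presented, so for this trial the new model would have to be labelled post hoc, with the change-score result kept beside it. It can be prespecified for the larger study.

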**DEVIATION OF FINAL MANUSCRIPT FROM PROTOCOL SUBMITTED TO REB**

***[name] did not participate in the study and so was not included in the manuscript as he did not meet authorship criteria. He was involved in initial discussions about the protocol and for this was included as an author for the abstract (please see “Knowledge translation for citation of published abstract).***

*Clinical co-ordinator (TBA)*

The clinical co-ordinator will be responsible for ensuring the administration for the overall conduct of the study including scheduling appropriate patients once they have been screened, assisting in REB submission and compliance, collecting outcome measures, entering data and overseeing completeness of data. Following training by the Elkie Adler Clinic’s physical therapist, the clinical co-ordinator will provide support and re-enforcement to caregivers as to the specific exercise regimens to be applied to patients.

**Feasibility**

The Elkie Adler Clinic has over 4,000 patient visits per yr, and serves patients with neurological impairments including dementia, multiple sclerosis, stroke, traumatic brain injury, Parkinson’s disease, and spinal cord injuries. Though it serves a broad population of outpatients distributed throughout the GTA and Ontario, it increasingly treats clients who reside in long-term care institutions, who constitute natural subjects for this study as they are referred to the clinic primarily for the indication that this study proposes to investigate. Both [name] and [name] have a large population of patients with cognitive impairments that would be eligible for the study (please refer to letters of support). As such, recruitment of 1-2 patients/month is a feasible target with recruitment completed within 6-12 months.

**Ethical considerations**

The protocol will be approved by the Baycrest Research Ethics Board. Study forms and the computerized study database will contain no personal identifiers. All paper forms will be kept in locked cabinets and all computerized files will be kept on password protected computers that will only be accessible to study personnel.

**Knowledge translation**

Study findings will be submitted for presentation at an international neurology meeting (e.g., American Academy of Neurology, American Neurological Association, Movement Disorders Society Congress, etc). Study findings will be submitted for publication in a high impact specialty or subspecialty journal, with preference given to open-access journals due to their enhanced availability to practicing clinicians.

***Study was presented at the 18th International Movement Disorders Congress in Stockholm Sweden June 11, 2014 and the abstract has been published (****[name], [name], [name], [name], [name], [name], [name]; Botulinum toxin treatment reduces involuntary postures and caregiver burden in people with advanced cognitive impairment [abstract]. Movement Disorders 2014;29 Suppl 1 :1107)*****

**Potential Impact/Significance of Study**

In these times of fiscal constraint, difficult decisions need to be made regarding resource allocation to optimize patient care. If the potential for this intervention is affirmed through well designed clinical trials, this would constitute an important, attractive, and likely cost-effective management tool. Our expectation is that the use of Botulinum toxin injections for management of paratonia in individuals with dementia is an intervention with the capacity to reduce care burden (including reduced time to perform ADLs), improve standard of care for dependent individuals, and potentially increase patient quality of life in this increasingly common condition.

